**Fig. 1 Fig1:**
[figure not shown]
Study flowchart

### Procedure

Patients presenting with trauma-related symptoms to participating mental healthcare centers in Paris (15 centers), Lille, Fort-de-France, Poitiers and Nice (2 centers) regions are informed of the study. After the study has been fully explained to them, interested patients are asked to sign the informed consent form. The clinician then formally investigates if the study requirements are fulfilled and determines patient eligibility. Based on the patients’ choice and their eligibility for the RT group, enrolled patients are then allocated to RT or TAU. The treatment begins within 7 days of enrolment. A series of six treatment sessions are set on a once a week basis, but with a margin of 4–15 days between sessions. The patients’ general practitioner is informed about their patient’s participation in the study. The symptom assessments are conducted for both groups at baseline, and then 7, 13, and 52 weeks after study inclusion.

### Clinicians training

A two-day course is provided to the participating clinicians by the first author ([name]). Clinicians are either medical doctors with a mental health background or practice, practicing residents and psychiatrists, or practicing psychologists. The first part of the training involves the proper identification of trauma-related disorders. The second part reviews the empirical evidence in favor of RI. The third part is practical and addresses propranolol prescription rules, role playing, RT procedures (see also Brunet et al., 2018) and research protocol information. Online clinical supervision is offered to each clinician via a private forum moderated by [name] as well as personalized telephone support with [name] or [name] regarding specific questions, on an as needed basis. Treatment adherence is monitored in the following way: selection of the index traumatic event, performance of a cardiogram (first session only), oral propranolol dosage relative to ideal body mass, ingestion of a light snack with the propranolol medication, heart rate and blood pressure at baseline and, following ingestion of propranolol, the participant’s side effects to propranolol, the time elapsed between propranolol ingestion and the beginning of the treatment session, the completion of a self-report PTSD symptom measure by the patient covering the previous week, the length (number of pages) of the trauma narrative, use of the first-person singular, and verb tense (present) of the trauma narrative, the inclusion in the trauma narrative of five or more descriptors (from a list) of peritraumatic physical reaction, whether the patient actually read aloud his or her full script, the designation to the therapist of the *hot spot* in the trauma narrative, the possibility to revise/supplement the trauma narrative at each treatment visit, the number (six) and duration (10–25 min.) of the treatment visits, the number of days between each treatment visit, as well as the lack of use of any other empirically-validated treatment method for PTSD by the treating clinician during the treatment sessions.

### Study treatments

Reconsolidation Therapy™ (RT) consists in actively recalling one’s *index* (i.e. worst/traumatic) event, using a specific memory reactivation protocol, under the influence of the ß-blocker propranolol, once a week, for 10–25 min with a therapist, over 6 consecutive weeks. More specifically, 1 mg/kg of oral propranolol (Inderal™/Avlocardyl™) based on ideal body mass index (BMI) is given at the treatment center 75 min (+/− 15 min) before the session. Once the session begins, the patients are asked to write (session 1) and read out-loud (sessions 1–6) a 1–2 pages narrative of their traumatic event. On subsequent sessions, the patients are asked if they wish to update or modify their narrative to include new/more detailed information thatg bothered them during the previous week. The trauma narrative, a description of the event and of the trauma’s *hot spot* (i.e. the most bothersome/unacceptable part of the event), includes at least five bodily sensations and is written in the first person singular, present tense [15].

Treatment as usual (TAU) involves receiving the PTSD treatment offered locally at this treatment center, whatever this treatment may be. In most centers, TAU was an SSRI (most commonly, paroxetine 20–60 mg started at the first treatment visit), and/or a form of psychotherapy, typically CBT, EMDR, supportive therapy or psychodynamic therapy [26–28].

### Instruments

The primary outcome for the effectiveness analysis is the difference between the group mean PTSD Checklist-Specific (PCL-S) score at inclusion (T0) minus the same score obtained at the one-year follow-up (T3). The PCL-S will be administered at baseline (T0), at each treatment session (t1-t6) and 1 week posttreatment (T1), 3-month follow-up after baseline (T2) and one-year follow-up after baseline (T3).

The reliable and valid PCL-S [32, 33] is a 17-item self-report scale that assesses DSM-IV-TR PTSD symptoms in the past week from the perspective of the patient. (No validated French PCL version compatible with the DSM-5 was available when the study began). The PCL-S ranges between 17 (no symptom) and 85 (maximum score). For study inclusion, a cut-off score of equal or greater than 44 is used, as done by others [34, 35] (Fig. 2).

**Fig. 2 Fig2:**
[figure not shown]
Evolution of the confidence interval according to the sample size and the delta PCL-S (green line: delta PCL-S above 30; red line: delta PCL-S below 30)

The Clinical Global Impression (CGI) scale is used as a global evaluation of the patients’ condition and symptom evolution. The CGI is composed of two parts: illness severity (CGI-S) and improvement (CGI-I), each of which is rated on a 7-point scale where 1 represents health (not ill/very much improved) and 7 represents illness (extremely ill/much worse). The CGI is administered by a clinician blind to the patient’s treatment modality.

*PTSD or adjustment disorder diagnosis and comorbidities*, are assessed with the MINI International Neuropsychiatric Interview (MINI-S), a structured diagnostic interview based on the DSM-5. PTSD, adjustment disorder, anxiety modules as well as lifetime and current depression, suicidality, obsessive-compulsive disorder, alcohol and substance abuse and dependence are assessed in order to report any comorbid disorders that are frequently associated with PTSD. The MINI-S is the new version of the MINI interview [36]; its validation in French is in progress at our center and elsewhere.

*Distress and dissociation at the time of trauma* are assessed with the reliable and valid Peritraumatic Distress Inventory (PDI) [37, 38] and the Peritraumatic Dissociative Experiences Questionnaire (PDEQ) [39, 40], respectively. The 13-item self-report PDI documents the recalled emotional responses experienced at the time of the trauma and, as such indexes the subjective severity of the trauma from the patient’s perspective. It ranges between 0 (no symptom) and 52 [41]. The 10-item self-report PDEQ measures the recalled dissociative reactions experienced during or immediately after the traumatic event and is an index of poor prognosis. Items are scored from 1 to 5 with a total score ranging between 10 (no symptom) and 50.

The primary outcome for efficiency (cost-utility) analysis is *Quality of life* at 12 months assessed with the reliable and valid EuroQol questionnaire (EQ-5D-5 L) [42, 43]. The EQ-5D-5 L assesses five health dimensions: mobility, self-care, usual activities, pain/discomfort and anxiety/depression. Each dimension is rated on five levels of severity [42, 43]. The utility value set for each score is available for the French population. These values will be used in the assessment of efficiency of RT. We will also use the 26-item self-report World Health Organization Quality of Life WHOQOL-Bref [44, 45], which measures the extent to which illness impairs the subjective wellbeing of patients at the time of the assessment. Each item scored 1–5 is summed and transformed into a 0 (poorest QOL) to 100 (best QOL) symptom score. The scale produces four main scores: physical, psychological, social relationship and environment.

*Costs related to healthcare utilization and work status* are evaluated with the MEDico-EConomic Questionnaire (MEDEC) adapted from the Client Service Receipt Inventory [46, 47] in order to meet the specificity of the French health system. This inventory collects retrospective information on health service utilisation in order to estimate illness related costs. It includes a history of hospitalization, sick leave, treatments received, medical consultations, as well as all paramedic consultations regardless of the reason.

This economic evaluation is conducted in accordance with the recommended methods of the HAS (*Haute Autorité de Santé* or French Health Authority) and the CHEERS (Consolidated Health Economic Evaluation Reporting Standards) [48].

*Social functioning* is evaluated with the Social Functioning Scale (QFS) [49]. The 16-item self-report QFS assesses the frequency and satisfaction with a number of social behaviours in a psychiatric adult population. Each item is scored from 1 to 5 with frequency and satisfaction scales ranges between 8 and 40 and a total range of 16 to 80 over the previous 2 weeks and is sensitive to change after treatment [49].

*General anxiety and depressive symptoms* are evaluated using the 25-item self-report Hopkins Symptom Checklist (HSCL-25) [50], which includes a subscale measuring anxiety and another measuring depression (each item is scored 1–4, and the total mean score also ranges from 1 to 4, with the clinical cut-off being set at 1,75). The total score is correlated with emotional distress of unspecified diagnosis, and the depression score is correlated with major depression as defined by the DSM-IV-TR [51].

### Statistical analyses

The clinical scores will be analyzed using an intention to treat (ITT) analysis: all patients allocated to RT or TAU will be analyzed. The collected data will be used to describe the 2 cohorts: the RT group and the TAU group. Variables will comprise socio-demographic parameters, duration of PTSD, psychiatric comorbidities, pre-morbid disorders, and co-prescriptions. As described above, the primary outcome for effectiveness analysis is based on the delta (T3 minus T0) of PTSD *symptom severity* (PCL-S). A first indicator will be the mean PCL- S difference between T3 and T0. The delta of EQ5D-5 L (T3 minus T0) examines efficiency from the health economic perspective.

A regression model will be used to calculate a second indicator based on the PCL-S values (t1-t6) collected between T0 and T1, allowing for the evaluation of PTSD symptoms evolution over time and its variation between individuals. A third indicator will be the rate of patients considered as treatment responders (PCL-S score < 44) at Week 7 (T1), Week 13 (T2) and Week 52 (T3). Mean and SD will also be computed for the delta of CGI score between T1 and T0. Missing data will be replaced using multiple imputation methods, provided that the data is missing at random or completely at random.

Additionally, in order to take into account the difference between the features of both cohorts (RT and TAU), we will use a propensity score of being allocated to RT to adjust the different model. For the secondary criteria, these propensity scores will be applied to the other scales used for the assessment.

Costs will be estimated from the point of view of society for the follow up period (1 year) without discounting, due to the study duration. We will estimate in each group the median cost, mean and 95% confidence interval (95%CI) using bootstrap replications because of distribution skewedness and calculate the cost difference. Health-related QOL is collected using the EQ-5D-5 L self-administered questionnaire at baseline, at 3 months and at 1 year. The utility values will be based on French tariffs. The efficacy of the intervention will be estimated by quality adjusted life years (QALYs), using the EQ-5D-5 L scores and the time between treatment sessions. The difference in QALYs is the difference in the area between the utility curves for the two groups. Between-group comparisons of QALYs and costs will be performed with the appropriate statistical tests for their distribution, with a significance threshold of .05 (two-sided test).

The incremental cost utility ratio is the difference in average total costs divided by the difference in average total QALYs. The joint comparison of costs and effects will use nonparametric bootstrapping with 1000 resamples and generate the scatterplot on the cost effectiveness plane as a well as an acceptability curve.

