## Methods

### Study design

This study is a two-arm non-randomized, multicenter controlled trial, comparing RT to TAU for the treatment of trauma-related disorders. As shown in Table 1, psychometric assessments are made at baseline, after 6 weeks of treatment, as well as 3 and 12 months following study inclusion. In order to enhance external validity this study protocol is implemented into the usual healthcare system in France. Patients are offered the choice of the intervention they wish to receive. The study protocol was approved by local ethics committee (*Comité de protection des personnes* for Ile de France VI #CPP/14–16), and regulatory agencies (*Commission nationale de l’informatique et des libertés* #GPR1713292F and *Agence nationale de sécurité du medicament.* We plan to include up to 400 participants with the possibility of stopping at the end of the pre-specified inclusion period if at least 200 receiving RT are enrolled.

**Table 1 Tab1:** Overview of measures and time of assessment

Instrument	Variable	T0	Treatment sessions						T1	T2	T3
			t1	t2	t3	t4	t5	t6			
Demographics	*Sociodemographic characteristics*	X									
PCL-S	*PTSD symptom severity*	X	x	x	x	x	x	x	X	X	X
CGI	*Global patients’ condition*	*	x	x	x	x	x	x	*	*	*
MINI-S	*Diagnosis and comorbidities*	X							X	X	X
PDI	*Severity of trauma exposure*	X									
PDEQ	*Peritraumatic dissociation*	X									
WHOQOL-BREF	*Quality of life*	X							X	X	X
EQ-5D-5 L	*Quality of life*	X							X	X	X
MEDEC	*Health service utilization*	X							X	X	X
HSCL-25	*Anxiety and depressive symptoms*	X							X	X	X
QFS	*Social functioning*	X							X	X	X

*Assessed by a clinician blind to the patient’s treatment modality

T0: baseline assessment

T1: posttreatment assessment (week 7)

T2: 3-month follow-up assessment

T3: one-year follow-up assessment

PCL-S: PTSD Checklist – Specific Version, CGI: Clinical Global Impression, MINI-S: Mini International Neuropsychiatric Interview for DSM-5, PDI: Peritraumatic Distress Inventory, PDEQ: Peritraumatic Dissociative Experiences Questionnaire, WHOQOL-BREF: World Health Organization Quality of Life (brief), EQ-5D-5 L: EuroQol Questionnaire, MEDEC: Medico-Economic Questionnaire, HSCL-25: Hopkins Symptom Checklist, QFS: Social Functioning Questionnaire

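### The QALY time basis and EQ-5D-5L visit list contradict Table 1, and the efficiency outcome appears in three forms that are not equivalent

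*Protocol article*

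**What the plan says.** **Time basis.** Under Statistical analyses, QALYs are to be estimated "using the EQ-5D-5 L scores and the time between treatment sessions". The next sentence treats the QALY difference as an area between the two groups' utility curves. Costs in the same section cover one year.

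**Visits.** The same section says: "Health-related QOL is collected using the EQ-5D-5 L self-administered questionnaire at baseline, at 3 months and at 1 year". Study design says that "psychometric assessments are made at baseline, after 6 weeks of treatment, as well as 3 and 12 months following study inclusion". Table 1 marks the EQ-5D-5L at T0, T1, T2 and T3 and leaves the six session columns empty for it. The Table 1 key puts T1 at week 7, and Procedure places assessments for both groups at baseline and weeks 7, 13 and 52.

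**Efficiency outcome.** The Background (Efficacy, effectiveness and efficiency) makes efficiency a co-primary aim and says it is typically assessed by cost-utility analysis. The outcome then takes these forms:
- Instruments: "The primary outcome for efficiency (cost-utility) analysis is" quality of life at 12 months on the EQ-5D-5L.
- Statistical analyses, first paragraph: "The delta of EQ5D-5 L (T3 minus T0) examines efficiency from the health economic perspective".
- Statistical analyses, cost paragraphs: QALYs over the year and an incremental cost-utility ratio (ICUR).
- Discussion: one of the main outcomes will combine cost and effectiveness.

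**The concern.** A QALY is utility accumulated over time, so it needs a utility at each node and the time between nodes. The stated time basis refers to occasions at which no utility is recorded. The stated visit list drops one occasion at which a utility is recorded. An analyst who follows the text cannot build the first and would discard data under the second. Both feed the denominator of the ICUR.

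The second matter is what answers the co-primary efficiency aim. A 12-month level, a 12-month change and a one-year accumulated QALY set against cost are different quantities. They can rank the arms differently, and the first two contain no cost. The article does not say how they relate, so a reader of the results could not tell which one the efficiency conclusion was meant to rest on.

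**Working it through.** The article gives no QALY, utility or ICUR figure, so there is nothing to reproduce. The check compares the schedules and works out what follows from them.

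**Inputs from the article.** EQ-5D-5L visits by Table 1, with weeks from Procedure: 0, 7, 13, 52. EQ-5D-5L visits by Statistical analyses: 0, 13, 52. Sessions by Procedure: six, weekly, with 4 to 15 days between them.

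**1. Time axis.** Six sessions have five gaps: 5 × 7 = 35 days nominally, and 5 × 4 = 20 to 5 × 15 = 75 days within the margin. The area under a one-year curve needs the intervals between utilities, which are 7, 6 and 39 weeks (sum 52). No EQ-5D-5L is scheduled at any session, so session gaps have no utilities to weight.

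**2. Weight of each visit.** Under the trapezoidal rule over 52 weeks, each visit's weight is half the sum of its adjacent intervals, divided by 52.
- Four visits: T0 3.5/52 = 0.0673; T1 (3.5 + 3)/52 = 0.1250; T2 (3 + 19.5)/52 = 0.4327; T3 19.5/52 = 0.3750.
- Three visits: T0 6.5/52 = 0.1250; T2 (6.5 + 19.5)/52 = 0.5000; T3 0.3750.

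Four-visit minus three-visit QALY = 0.125·u(T1) − 0.0577·u(T0) − 0.0673·u(T2). The straight line from T0 to T2 at week 7 is (6/13)·u(T0) + (7/13)·u(T2), and 0.125 times that gives the last two terms. So the change is exactly 0.125 × d, where d is the week-7 utility minus that line.

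**3. Size between arms.** The effect on the QALY difference is 0.125 × (d in RT minus d in TAU). The article gives no utilities, so this is a range of assumptions:
- equal departures: 0
- difference of 0.05: 0.00625 QALY
- difference of 0.10: 0.0125 QALY

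Example within one arm, with assumed utilities 0.60/0.80/0.80/0.80: four visits give 0.0673 × 0.60 + 0.9327 × 0.80 = 0.7865; three visits give 0.125 × 0.60 + 0.875 × 0.80 = 0.7750.

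**4. Are the efficiency quantities interchangeable?**
- Level and change against QALY: the assumed paths 0.60/0.80/0.80/0.80 and 0.60/0.60/0.60/0.80 share the 12-month level (0.80) and the T3 minus T0 change (0.20). Their four-visit QALYs are 0.7865 and 0.625 × 0.60 + 0.375 × 0.80 = 0.6750, a gap of 0.1115.
- Level against change: the unadjusted between-arm difference in level minus that in change is [RT(T3) − TAU(T3)] − {[RT(T3) − RT(T0)] − [TAU(T3) − TAU(T0)]} = RT(T0) − TAU(T0). That is the baseline imbalance, and patients here choose their arm.

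**The case against.** The strongest reply is that the intent can be recovered. The one-year cost horizon and the sentence on the area between utility curves point to time between assessments, so the session wording is almost surely a slip. That stands. A reader might infer that the QALY would cover only the 20 to 75 days spanned by the sessions. The documents do not support this, because without utilities at sessions such an analysis cannot be run. Those days show the incompatibility; they are not a likely error.

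Other stronger readings also fail:
- *TAU has no session calendar.* Procedure sets the six weekly sessions without limiting them to RT, and the session columns of Table 1 are not specific to an arm. Study treatments leaves the content of TAU open but does not say that it lacks sessions.
- *Week 7 is where the arms differ most.* Nothing shows this. The Background gives a mean SSRI response time of 4 to 6 weeks and psychotherapy courses of 6 to 12 sessions once or twice weekly, so much TAU response could have occurred by then.
- *Omitting T1 removes a large share of the QALY gain.* Any such percentage needs an assumed gain as well as an assumed departure, and the article gives neither.
- *Three competing primary outcomes are declared.* Only Instruments uses the word primary. Statistical analyses says that the change examines efficiency and never calls the QALY or the ICUR primary. The ICUR formula and the bootstrap are specified, which limits later choice.

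A condensed article may also leave trapezoidal detail to a fuller document. That does not excuse a stated time basis and visit list that conflict with its own Table 1. Propensity adjustment may shrink the gap between level and change, but it does not say which quantity is primary.

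**Conclusion.** The point holds as a set of contradictions in the text.

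The time basis for QALYs is wrong as written, and the three-visit list conflicts with Table 1. The week-7 utility carries 0.125 of the one-year weight when all four visits are used. The effect of omitting it on the between-arm QALY is probably modest: zero if both arms depart equally from the T0–T2 line, and about 0.006 to 0.0125 QALY if the departures differ by 0.05 to 0.10. These figures rest on assumed utilities and trapezoidal interpolation.

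The outcome for the efficiency aim matters more. The 12-month level (the only version labelled primary), the T3 minus T0 change, and the QALY with its ICUR are not equivalent, and their relation is not stated. In a non-randomised comparison the first two already differ by any baseline imbalance, before adjustment. It does not follow that the economic analysis is unusable or open to free choice. The conclusion is that a co-primary aim lacks one clearly identified quantity.

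**What to change.** 1. In Statistical analyses, replace the reference to treatment sessions with the time between EQ-5D-5L assessments.
2. In the same section, list the EQ-5D-5L at T0, T1, T2 and T3, as in Table 1, and compute the area under the French-tariff utility curve over all four visits in the same way in both arms.
3. Reconcile Instruments and Statistical analyses by naming one primary efficiency outcome. The one-year QALY with its ICUR fits the stated cost-utility aim and the Discussion's description of an outcome that combines cost and effect. The 12-month EQ-5D-5L value and its change from baseline then become secondary. Another choice is possible, provided that it is stated once and used throughout.

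The cost is a few reworded sentences. No new data are needed, because the T1 EQ-5D-5L is already in the schedule.

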### Efficacy, effectiveness and efficiency

As summarized by Kim [30], efficacy is the extent to which an intervention works under ideal circumstances while effectiveness assesses whether an intervention works when provided under usual circumstances of healthcare practice. Research on effectiveness is also described as pragmatic trials (see Additional file 1) [31]. Pragmatic trials have several characteristics: 1) patient eligibility and recruitment should reflect routine practice; settings should reflect the care facilities available to a diverse population; 2) the intervention should be provided by normal staff with routine training; 3) intensity of follow-up should be similar to typical follow-up in usual care; 4) primary outcome should be directly relevant to participants and all patients should be included in the analysis of the primary outcome; 5) outcome measures are patient-centered and incorporate broad measures of health. Finally, efficiency refers to the ability to achieve a therapeutic goal using a lesser amount of time and resources than what is typically observed. Typically, efficiency is assessed by cost-utility analysis.

The co-primary aims of this pragmatic trial are to evaluate the effectiveness and the efficiency of RT therapy, as deployed in a post-terrorist attack real-world setting. Specifically, we wish to explore the feasibility of implementing in routine practice an innovative treatment for PTSD on a large scale and in a short period of time; to evaluate the acceptability of the treatment by the clinicians and from the patients’ perspectives; to assess the efficacy of RT; to determine its cost-utility compared to treatment as usual (TAU) over a 1-year period.

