### Eligibility criteria

Participants will be at least 18 years old without any upper age limit. Eligible participants must read and speak French, have a DSM-5 diagnosis of PTSD, adjustment disorder or any other specified trauma-related disorder. They must have a symptom score above 43 on the PTSD Checklist [32] and be at least moderately ill according to the Clinical Global Impression scale. They must not have a severe mental or neurological disorder (i.e., a history of bipolar or psychotic disorder, acute suicidal, homicidal, or self-injuring intentions, a traumatic brain injury in the last 5 years, an alcohol or substance dependence disorder), nor be involved in trauma-related litigation. Pregnant or breastfeeding women cannot participate in the trial for security reasons. In addition, to participate in the RT group, patients taking psychotropic medications must be on a stable dosage for at least 2 months, they must not use any medications that involve a dangerous interaction with propranolol, or have a resting heart rate inferior to 55 beats per minute, or a resting systolic blood pressure below 100 mmHg; any other contraindicating medical condition, as determined by the study physician (Fig. 1).

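### The co-primary cost-utility contrasts are written as crude group differences although patients choose their arm; the planned propensity score and the baseline utility and cost data are not carried into them

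*Protocol article*

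**What the plan says.** Allocation (Procedure): "Based on the patients’ choice and their eligibility for the RT group, enrolled patients are then allocated to RT or TAU". The RT arm has entry limits that TAU lacks (Eligibility criteria): "In addition, to participate in the RT group, patients taking psychotropic medications must be on a stable dosage for at least 2 months", followed by limits on interacting drugs, heart rate, blood pressure and other contraindications.

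Status of the economic question (Efficacy, effectiveness and efficiency): "The co-primary aims of this pragmatic trial are to evaluate the effectiveness and the efficiency of RT therapy". Under Instruments: "The primary outcome for efficiency (cost-utility) analysis is *Quality of life* at 12 months", measured with the EQ-5D-5L.

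Economic analysis (Statistical analyses, cost paragraphs). The QALY contrast is defined in one sentence: "The difference in QALYs is the difference in the area between the utility curves for the two groups". On testing, at a two-sided 0.05 level, the plan then commits to this: "Between-group comparisons of QALYs and costs will be performed with the appropriate statistical tests for their distribution". The ratio has its own definition in the next paragraph: "The incremental cost utility ratio is the difference in average total costs divided by the difference in average total QALYs". The cost-effectiveness plane and acceptability curve come from 1000 nonparametric resamples. Group mean costs get bootstrap confidence intervals.

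Confounding (same section, earlier): a propensity score for being allocated to RT is to adjust the models, and then "For the secondary criteria, these propensity scores will be applied to the other scales used for the assessment". The Discussion adds, in general terms, that comparing the two cohorts will involve such a score. The EQ-5D-5L change from T0 to T3 is also listed as an efficiency measure. Table 1 shows EQ-5D-5L and MEDEC both collected at T0.

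**The concern.** When patients select their arm, and some can enter only TAU, the arms may differ at baseline in utility, in health-service use and in what drives both. The article recognises this for the comparison of the cohorts and plans a propensity score. The cost-utility paragraphs, however, give explicit formulas, and each is a difference between two raw group summaries with no model that a propensity score or covariate could enter. An analyst following them literally would produce unadjusted results.

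Two baseline quantities matter most. The area under the utility curve contains the T0 utility and whatever part of a T0 difference persists, so a starting advantage would be counted as QALYs gained. Total cost over the year likewise carries persistent differences in service use; MEDEC records consultations whatever their reason.

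The ICUR, the plane and the acceptability curve all rest on these two differences, so a co-primary conclusion could partly describe who chose RT. Separately, choosing the cost test by distribution leaves open a test that does not address the difference in mean costs, which is the numerator of the ICUR.

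**Working it through.** **What can be reproduced.** The article gives no precision figure for QALYs, costs or the ICUR. Its only sizing figure is for the PCL-S: 30 ± 1.96 × SD/√200 equals 27 to 33 at SD 21.65, inside its stated 15–25. That figure does not bear on this point.

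**Does the planned adjustment reach the economic contrasts?**
- The sentence on adjusting the models comes before the cost paragraphs, which do not refer back to it.
- The extension concerns secondary criteria and measurement scales. Costs are not a scale, and the efficiency outcome is labelled primary.
- The Discussion sentence is general and follows directly on the symptom-severity regression.
- The T3 minus T0 change in EQ-5D-5L uses baseline utility, but it is a separate quantity and does not feed the QALY area, the ICUR or the bootstrap.

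**Weight of baseline in the QALY.** The cost paragraphs list EQ-5D-5L at 0, 3 and 12 months. Trapezoid weights in years:
- T0: 0.25/2 = 0.125
- 3 months: 0.25/2 + 0.75/2 = 0.50
- 12 months: 0.75/2 = 0.375

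**Bias with no treatment effect.** Let d be the T0 utility imbalance and p the share persisting at later visits. Then bias = d × (0.125 + 0.875p). Both d and p are assumptions; the article gives neither. With d = 0.05:
- p = 0: 0.05 × 0.125 = 0.006
- p = 0.5: 0.05 × 0.5625 = 0.028
- p = 1: 0.05 × 1 = 0.050

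Table 1 also lists an EQ-5D-5L at week 7. If that visit is used, the T0 weight is 3.5/52 = 0.067, and p = 0.5 gives 0.05 × (0.067 + 0.933 × 0.5) = 0.027, practically the same.

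Over a wider assumed range:
- d = 0.03, p = 0.5: 0.03 × 0.5625 = 0.017
- d = 0.10, p = 0.7: 0.10 × (0.125 + 0.6125) = 0.074

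**Effect on the two-sided 5% test.** Assume 200 per arm (the article fixes no ratio) and a QALY SD of 0.20. The standard error is 0.20 × √(1/200 + 1/200) = 0.020. A bias of 0.028 is then 1.41 standard errors, and the test rejects in about 29% of trials with no effect. At 300:100 it is about 23%. Across d = 0.03–0.10, p = 0.5–0.7 and SD 0.15–0.25, at 200 per arm, the rate runs from 10% to 99.8%. The range is wide because it depends almost entirely on the assumptions.

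**Does the change score solve it?** Its remaining bias is d × (p − 1). With d = 0.05 and p = 0.5 it is −0.025; with d = 0.05 and p = 0.7 it is −0.015. It over-corrects when persistence is below 100%, and it leaves the QALY area untouched.

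**Costs.** The article gives no cost figures, so no size can be shown.

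**The case against.** The strongest reply is that the cost paragraphs are silent on adjustment rather than opposed to it. The propensity-score sentences in Statistical analyses and the Discussion are broad enough to cover the economic comparison, and EQ-5D-5L is one of the assessment instruments. The article also commits to the French Health Authority's methods and to CHEERS, and an unseen analysis plan may hold the detail.

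Much of this stands, and it rules out several stronger readings that a reader might infer:
- **That the plan has no confounding adjustment for cost-utility.** Not supported, given those general statements and the separate EQ-5D-5L change score.
- **That the contrasts are in fact confounded, or that the ICUR would change sign.** Not supported. The documents show exposure to bias but give neither its size nor its direction.
- **That costs will be compared with a rank test.** None is named, and bootstrap intervals for group mean costs are already planned. The wording only leaves such a test possible.
- **That propensity weighting is planned.** The article speaks of adjustment and does not say by what technique.

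What the reply does not remove is that the cost paragraphs go beyond silence: they define each contrast, and the definitions are crude. If the broad reading is intended, it does not fit those formulas, and the two need to be reconciled.

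**Conclusion.** The point holds as a gap between a general intention to adjust and explicit unadjusted formulas for a co-primary analysis. The QALY difference, cost difference, ICUR and bootstrap, as written, are exposed to confounding by arm choice and to baseline imbalance in utility and cost.

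The illustrative bias of 0.028–0.050 QALY rests on an assumed T0 imbalance of 0.05, 50–100% persistence, visits at 0, 3 and 12 months, and no treatment effect. Most of it comes from the persistence assumption: with none, it is 0.006. The true size cannot be derived from the article.

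This is an improvement worth making, since the data are already collected and a better-specified method is available. It does not show that the eventual result is wrong.

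**What to change.** In the cost paragraphs of Statistical analyses:
1. State that the propensity score described earlier in that section and in the Discussion also applies to costs and QALYs.
2. Estimate the QALY difference by regression on arm plus T0 EQ-5D-5L utility, and the cost difference by regression on arm plus T0 MEDEC cost, together with the propensity adjustment. The baseline terms handle imbalance in those two quantities; the score is still needed for other measured confounders.
3. Use the adjusted mean differences as numerator and denominator of the ICUR.
4. Repeat the propensity estimation and the adjustment within each of the 1000 resamples, so that the plane and acceptability curve describe the adjusted contrasts.
5. Base the between-group inference on costs on the difference in arithmetic means with a bootstrap confidence interval, so that it matches the ICUR numerator.

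The cost is a few sentences of text and modest extra programming. No new data are needed, because T0 EQ-5D-5L and T0 MEDEC are already in Table 1. Unmeasured confounding would remain and should be acknowledged when the ICUR is reported.
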